## Abstract

**Background:**

After root canal treatment, most tooth defects need to be restored. Onlay restoration is widely used to restore dental defects. Endocrown is a new type of onlay; however, dentists have yet to obtain a full understanding of the clinical effects of marginal forms of endocrowns. Here, we present a multicenter protocol to compare the clinical efficacy of two marginal forms (flat and 90-degree shoulder) for tooth restoration. The efficacy will be evaluated by marginal fit, marginal discoloration, and integrity of restoration.

**Methods:**

The proposed flat and 90-degree shoulder marginal endocrown assessment trial is an open-label, parallel-group, multicenter randomized controlled trial involving two hospitals. A total of 200 patients will be included in this trial, and the following patient inclusion criteria will be applied: good oral hygiene habits, no periodontal diseases, receipt of standard root canal treatment, and need for endocrown restoration. Patients will be enrolled after providing signed informed consent and will be divided into two groups (flat and 90-degree shoulder endocrown) in accordance with a random number table. Treatment allocation will be balanced (1:1). Endocrowns will be cemented by dual-cured luting composite. Clinical evaluations will be performed at baseline and at 24 months after treatment in accordance with modified US Public Health Service criteria by two independent evaluators. The primary outcome will be marginal fit; secondary outcome measures will include debonding, marginal discoloration, and integrity of restoration. All acquired data will be analyzed by an independent statistician. Wilcoxon one-sample tests will be used for intra-group comparisons, and Wilcoxon two-sample tests will be used for inter-group comparisons. The Bonferroni method will be used to correct for multiple comparisons, and hierarchical logistic regression will be applied to determine central effects.

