### Methods

This is a multicenter, randomized, open-label superiority trial with two balanced parallel arms. The participants will be recruited from the Departments of Conservative and Endodontic Dentistry in Nanfang Hospital of Southern Medical University and the Guanghua School of Stomatology of Sun Yat-sen University. The schedule of enrollment, interventions and assessments is showed in Fig 2.

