### Dropout criteria

Poor clinical complianceVoluntary withdrawal from the trial by the patient

According to the software nQuery Advisor + nTerim 3.0, a sample size of 160 patients (80 for each group) should be recruited [30]. To allow for 20% attrition, the recruitment sample size for this trial will be 200 patients (100 in each group).

Upon fulfilment of the selection criteria, 200 eligible participants will be randomly divided into intervention and control groups in a 1:1 allocation ratio. Randomization will be performed in accordance with a random list of numbers generated by the Department of Biomedical Statistics of Southern Medical University. Five dentists will participate in this study and all of them will have received standardized training in endocrown restoration before the study begins. The number of cases assigned to each dentist is unknown and will vary because of factors outside the control of the study. These five dentists will not be involved in observations or data collection during the clinical evaluations.

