#### Primary outcome analysis

Wilcoxon one-sample tests will be used for intra-group comparisons, and Wilcoxon two-sample tests will be used for inter-group comparisons. The Bonferroni method will be used for multiple comparisons, and hierarchical logistic regression will be used to detect central effects.

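### No balancing of the arms within hospital is stated, and the primary Wilcoxon test ignores hospital, so chance differences in hospital mix enter the main comparison as avoidable noise

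*Protocol article*

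**What the plan says.** The protocol article describes the allocation sequence twice. The Methods part of the Abstract says that patients are divided "in accordance with a random number table". The randomisation paragraph, which stands under the heading Dropout criteria, says: "Randomization will be performed in accordance with a random list of numbers generated by the Department of Biomedical Statistics" of the university. Neither place mentions blocks, strata, minimisation or separate lists for the hospitals.

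The intended result is stated more firmly. The Abstract has "Treatment allocation will be balanced (1:1"), the Methods section calls the trial a "multicenter, randomized, open-label superiority trial with two balanced parallel arms", and the randomisation paragraph gives 100 patients per group.

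The Abstract describes a "multicenter randomized controlled trial involving two hospitals". The randomisation paragraph adds that five dentists will treat the patients and that their caseloads are not controlled. Under Primary outcome analysis, the between-group comparison is a Wilcoxon two-sample test, and "hierarchical logistic regression will be used to detect central effects". I read this last phrase as meaning effects of centre.

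**The concern.** Hospital is a plausible source of variation. The primary outcome is a four-grade rating of marginal adaptation made with a probe (Table 1), so it may depend on case mix, operator and rater, and each of these can differ between hospitals.

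As the article is written, neither the design nor the primary test uses hospital. A list that is balanced in total can still place more of one hospital's patients in one arm. An unstratified Wilcoxon test then carries part of any hospital difference into the treatment comparison. The regression is described as a way to find centre effects, not as an adjustment of the treatment comparison. At stake is some precision in the primary result, and an awkward reading of it if the hospitals turn out to differ and the arms are unevenly mixed.

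**Working it through.** **Inputs from the article.** Two hospitals; 160 patients needed (80 per group); 20% attrition; 200 recruited (100 per group); 1:1 allocation.

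**Assumptions.** The article does not give the split of patients between hospitals, so I take the smaller hospital as 100, 60 or 40 of the 200. A 20-point difference between hospitals in grade-A rate and an overall grade-A rate of 80% are illustrations only.

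**1. The article's own figure.** 160 / (1 − 0.20) = 200, or 100 per group. It reproduces.

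**2. List fixed at 100:100, not split by hospital.** Let m be the size of one hospital and X the number of its patients in one arm. Then X is hypergeometric (200 patients, 100 in the arm, m drawn), with SD = √[m × 0.25 × (200 − m)/199]. The arms differ in hospital mix by D = (2X − m)/100.

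For m = 100: SD(X) = √(100 × 0.25 × 100/199) = 3.54, so SD(D) = 2 × 3.54/100 = 7.1 points.

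| Size of one hospital | P(mix differs by ≥ 10 points) | P(mix differs by ≥ 14 points) |
|---|---|---|
| 100 | 20.3% | 6.6% |
| 60 | 16.5% | 4.4% |
| 40 | 11.1% | 2.1% |

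With m = 100, the 95% range for one arm within that hospital is 43 to 57.

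**3. Effect on the arm difference.** Shift = mix difference × hospital difference in grade-A rate.
- 0.10 × 20 points = 2.0 points
- 0.14 × 20 points = 2.8 points

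**4. Against ordinary sampling error.** With 80 evaluable per arm and a grade-A rate of 80%, the standard error of the arm difference is √(2 × 0.8 × 0.2/80) = 6.3 points. The shifts are therefore 2.0/6.3 = 0.32 and 2.8/6.3 = 0.44 of a standard error.

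**5. Gain from the stratified test.** In a simulation with assumed rates and 80 per arm, the hospital-stratified Wilcoxon test kept type I error near 5%, lost nothing when the hospitals did not differ, and gained about 1 point of power when they did.

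**6. If the list were simple randomisation.** The article does not say that it is. In that case the number in one arm is Binomial(200, 0.5): exactly 100:100 has probability 5.6%, the 95% range is 86 to 114, and a 90:110 or worse split has probability 17.9%. Even at 114:86 the relative efficiency is 4 × 114 × 86/200² = 0.980, so unequal totals would cost little.

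**The case against.** The strongest reply is that the point argues from silence. The article names the source of the random numbers and who prepares the list, not how the list is built. A list from a statistics department can be blocked, stratified or a fixed set of 100 plus 100, and a condensed article commonly leaves such detail to the full protocol. This stands to the extent that one cannot say the list is unrestricted.

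Two stronger readings are tempting, and the document supports neither.
- **A reader might infer that 100 per group is not assured.** That follows only under simple randomisation, which is nowhere stated and sits badly with the repeated statement of balanced arms.
- **A reader might infer that the sponsor expects the hospitals to differ.** The article plans to look for centre effects, which is routine in a multicentre trial and is not a forecast.

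It is also fair to say that the hierarchical regression gives centre some place in the primary analysis, that the effect is small, and that an unstratified test remains valid. What the reply does not remove is that the stated primary between-group test leaves hospital out, while nothing stated in the design secures balance on it.

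**Conclusion.** The point holds as an improvement worth making, not as an error that threatens validity. Within-hospital balance is not shown to be secured, and the primary test does not compensate. Under a fixed 100:100 list, a mix difference of 10 points or more has probability between 11% and 20% across the hospital sizes assumed, and the resulting shift is under half a standard error even at 14 points. Randomisation stays unbiased and type I error is not at risk; the loss is precision. The size rests on the assumed hospital split and on the assumed 20-point hospital difference. If the hospitals do not differ, there is no loss.

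**What to change.** **Analysis.** Replace the two-sample Wilcoxon test for the primary between-group comparison with a Wilcoxon test stratified by hospital (van Elteren). This costs one sentence and no patients, and it covers everyone, including those already randomised.

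**Randomisation.** First establish how the existing list was built.
- If it is already stratified by hospital, say so in place of the reference to a random number table; nothing else in the scheme need change.
- If it is not, have the same department issue one 1:1 list per hospital, in permuted blocks of varying and undisclosed size, for patients still to be randomised. The arm difference within a hospital arising under the new list is then at most half the largest block: for an assumed block size of 4, at most 2 per hospital and 4 overall. The sample size stays at 200.

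**Costs and limits.** This takes a new list and a short amendment. Blocking makes allocation slightly easier to predict in an open-label trial, which varying undisclosed block sizes limit. Recruitment was under way (Trial status), so a new list cannot correct imbalance among patients already allocated; for them only the stratified analysis helps. Because a class A marginal rating after restoration is an inclusion criterion, the numbers finally included per arm may still differ from those randomised under any scheme.

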**Discussion:**

The results of this trial will provide a clinical basis for clinicians to restore teeth by endocrowns and to improve long-term restoration for patients.

**Trial registration:**

ClinicalTrials.gov identifier: NCT03398395. Registered on 12 January 2018.

**Electronic supplementary material:**

The online version of this article (10.1186/s13063-019-3530-1) contains supplementary material, which is available to authorized users.

## Background

Pulpal and periapical diseases are the main causes of tooth loss. Root canal treatment (RCT) is the only effective means for treating these diseases. However, in the absence of coronal restoration, failure of RCT is commonly seen. Contamination of the root canal system by saliva, which is referred to as “coronal leakage” or “coronal microleakage”, is a potential cause of endodontic failure [1]. Tooth fracture is another cause. Indeed, teeth are vulnerable to fracture after RCT, the main reasons for which are as follows: (1) Dentin regeneration ceases once secondary dentin and tertiary dentin are interrupted. (2) In some cases, considerable loss of dental tissues has occurred because of deep caries, abrasion, or trauma [2]. (3) Tooth structure is weakened during RCT. As treated teeth are prone to fracture, especially in the coronal region of the posterior teeth, it is very important to restore the teeth within a certain time period after RCT. Moreover, coronal restoration can prevent reinfection of the root canal system or periapical area.

There are many ways to restore teeth after RCT, such as composite resin direct filling, inlay restoration, onlay restoration, full crown restoration, and post-core crown restoration [3]. In onlay restoration, one or more cusps of tooth are covered. This technique not only provides superior aesthetics but also minimizes the loss of healthy tooth tissue, making it an attractive treatment choice for posterior teeth with extensive cavities due to caries [4]. Moreover, by covering more than one tooth cusp, onlay provides a favorable distribution of stress, reducing the fracture risk of tooth or restoration or both. Ceramic onlay restoration showed promising results, yielding a 92.5% success rate, in a 4-year investigation of extensively restored, endodontically treated molars [5]. These observations suggest that onlay restorations are an optimal approach to restoring posterior teeth after RCT.

Endocrown is a new type of onlay with a retainer in the pulp cavity [6, 7]. It consists of a cervical margin in the form of a butt joint and a preparation of the pulp chamber. The endurance and stability of the restoration derive from the adhesion of cementation and increased stress sharing as well as the interface provided by the pulp cavity retainer [8]. This restoration method is not only effective for preserving residual tooth tissue but also suitable for severely damaged molars or premolars after dental pulp treatment [9]. Compared with post-core crown techniques, endocrown restoration is simpler because of the core-crown integrity; furthermore, no post is needed, reducing the risk of root fracture [10]. Post-core crown restoration is aimed at strengthening residual dental hard tissue and replacing missing dental tissue. The resistance of the tooth cervix is not enhanced, and the post only provides the retaining force for the crown [11]. Furthermore, post-core crown restoration can present additional risks, such as canal perforation and root fracture. Full crown restoration is also widely performed. A finite element analysis of a full crown and endocrown revealed that the endocrown was superior to the traditional full crown [12]. According to biomechanics, the strength of the dental tissue depends on the amount of dental hard tissue and its internal strength and anatomical characteristics. The characteristics of dental tissue are affected by caries, the preparation of the cavity, the path of access to the canals, and the enlargement of the root canal. However, Dietschi et al. showed that the effects of endodontic treatment on dental biomechanical properties are limited [13]. A three-dimensional finite element study showed that the stress distribution on enamel, dentin, and adhesive surface was smaller for endocrown than for all-porcelain onlay and traditional full crown [14, 15]. In addition, several experiments showed that endocrown had greater fracture resistance than traditional completed crown [14–16]. A retrospective study of endocrown restorations reported a clinical success rate of 94–100% [17] and demonstrated that the retention effect of endocrown restoration was superior to that of traditional full crown restoration. Endocrown restoration can preserve residual tooth tissue to a greater extent than can other restoration methods. It is especially useful for teeth with a low occlusogingival distance that have insufficient retention ability for a full crown.

Studies have shown that the type of marginal form has a significant effect on the prognosis of prostheses after RCT and restoration with full crowns [18–20]. The study by Taha et al. showed that adding a 1-mm shoulder finish line can increase the endocrown’s fracture resistance. However, further investigations, especially on fatigue behavior, are needed [21]. The restoration ability of endocrowns is affected by the bonding surface and the amount of residual tooth tissue [22]. The enamel layer distribution of the teeth bases, which determines the composition of the bonding surface as well as the residual amount of dental tissue, varies according to the preparation of the different marginal forms of endocrowns. A flat endocrown shows more residual tooth tissue and less bonding area, whereas a 90-degree shoulder endocrown leads to a larger bonding area and less residual tooth tissue. Whether there is a significant difference in restorative effect between these two forms is difficult to predict. Therefore, two common marginal forms of endocrowns will be designed in this study to observe their restoration effects (Fig. 1).

**Fig. 1 Fig1:**
[figure not shown]
Schematic representations of the two marginal forms of endocrown. A. Ninety-degree shoulder endocrown (intervention group). B. Flat endocrown (control group).

CAD/CAM is a type of computer-aided design and manufacturing software. The dental CAD/CAM system is used to collect imaging data of digital impressions through a built-in camera and does not require the intermediate links of traditional restoration systems, such as preparing molds and fillings. Therefore, this system can avoid possible errors during milling with numerical control machine tools. Because of its advantages in precision and clinical restoration, it is increasingly favored by patients and dentists [23, 24]. In recent studies, the system was used to successfully prepare complex prostheses that cannot be produced by traditional methods and was found to significantly shorten the production time of restorations [25].

Along with the rapid innovations in digital dentistry, additional chair-side CAD/CAM materials have been developed. According to the latest classification system, all-ceramic and ceramic-like restorative materials can be categorized into three groups, depending on the phase or phases present in their chemical composition: (1) glass-matrix ceramics, (2) polycrystalline ceramics, and (3) resin-matrix ceramics. All three types offer good aesthetic performance, mechanical properties, and biocompatibility [26, 27]. Glass-matrix ceramics are non-metallic inorganic ceramic materials that contain a glass phase and a dispersed crystalline phase (crystals) and are divided into three subgroups: feldspathic ceramics, synthetic ceramics, and glass-infiltrated ceramics. Synthetic ceramics can effectively prevent the expansion of cracks and improve the strength and cutting performance of the materials because of the greater presence of the crystalline phase than of the glass phase. Leucite-reinforced lithium disilicate and zirconia-reinforced lithium silicate ceramics are representatives of synthetic glass ceramics. Lithium disilicate ceramic (IPS e.max CAD, Ivoclar Vivadent, Amherst, NY, USA) is composed of about 70 vol.% of crystalline phase incorporated in the glassy matrix. The intermediate crystalline phase or “blue” state has 130 ± 30 MPa flexural strength, and the final flexural strength can reach 360 ± 60 MPa. It is widely used in clinical practice because of its good flexural strength and shade; however, it is also disadvantageous because the 15–20% contraction of the material after polymerization may lead to a reduction in the density between the onlay and teeth during the second sintering process [28]. Zirconia-enhanced lithium silicate glass ceramic (VITA SUPRINITY, VITA Zahnfabrik, Bad Säckingen, Germany) contains lithia (15–21 wt.%) and zirconia (8–12 wt.%) (about 10 times more zirconium dioxide than in traditional CAD/CAM glass ceramic). Its flexural strength can reach 450 MPa after glazing. Its ultrafine (0.5-μm) granules guarantee a homogeneous material structure to avoid polymerization shrinkage during the second sintering step. In addition, it has good emulsion fluorescence, which ensures an improved clinical polishing effect [29]. Experimental studies showed that VITA SUPRINITY had greater fracture toughness, flexural strength, elastic modulus, and hardness than disilicate glass ceramics.

Despite its advantages, VITA SUPRINITY has seldom been used in the design of different marginal forms of endocrowns. Therefore, we will use it as the experimental material in this study based on the dental CAD/CAM system.

## Methods and design

### Hypothesis

For this study, we hypothesize that the restorative effect of the 90-degree shoulder endocrown will be superior to that of the flat endocrown restoration.

### Objective

The objective is to compare differences between the two marginal forms of endocrowns (i.e., 90-degree shoulder and flat) by assessing the firmness, comfort, and durability of dental restorations after RCT using VITA SUPRINITY blocks designed and manufactured using a chair-side CEREC CAD/CAM system (Dentsply Sirona, Bensheim, Germany).

### Methods

This is a multicenter, randomized, open-label superiority trial with two balanced parallel arms. The participants will be recruited from the Departments of Conservative and Endodontic Dentistry in Nanfang Hospital of Southern Medical University and the Guanghua School of Stomatology of Sun Yat-sen University. The schedule of enrollment, interventions and assessments is showed in Fig 2.

**Fig. 2 Fig2:**
[figure not shown]
SPIRIT (Standard Protocol Items: Recommendations for Interventional Trials) Figure

### Inclusion criteria

The patient is healthy and is 18–60 years old and has molar teeth and tooth root apex without evident damage and no root fracture, as determined by x-ray.The patient has three or four walls of intact tooth tissue after complete root canal therapy.The patient has good oral hygiene.The patient has signed an informed consent form.The patient is not participating in any other clinical trial.The patient has received a class A assessment according to the modified US Public Health Service (USPHS) criteria for marginal adaptation after restoration.

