### The intervention group

The intervention group will receive 90-degree shoulder endocrown restoration. The restoration will be completed by the following steps: (1) All decayed or damaged areas of the tooth will be removed, and occlusal anatomical reduction of 2.0 mm will be performed to form a 90-degree rounded shoulder margin. Gutta-percha will be removed to a depth not exceeding 2 mm and sealed with composite resin. The undercuts of the tooth cavity will be blocked out with a nano-hybrid composite resin, which will serve as a base material. A 2- to 5-degree divergence of the vertical walls will be prepared with a conical flat-end diamond bur. (2) A chair-side CEREC CAD/CAM system will be used to mill VITA SUPRINITY blocks to obtain the prosthesis. (3) Cementation, occlusion adjustment, and polishing will be performed. (4) Patients whose affected tooth receives a class A assessment according to the modified USPHS criteria of marginal adaptation will be included in this trial.

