### The control group

The control group will be treated with flat endocrown restoration. In the first step of the restoration, all of the decayed or damaged areas of the tooth will be removed, and occlusal flat reduction of 1.5–2.0 mm will be achieved. The subsequent steps will be the same as those for the intervention group.

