## Discussion

This trial will help clinicians provide their clients with evidence-based options regarding marginal forms of endocrowns. However, owing to limitations associated with dental defects after RCT, the 90-degree shoulder endocrown is not suitable for all tooth restorations. Therefore, the selection of marginal forms should be based on the conditions of the dental defects.

This randomized clinical trial (see SPIRIT check list the Additional file 1) may lead to an improvement in the survival rate of restorations for patients. For researchers, it may provide input for further research concerning the marginal forms of endocrowns.

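### Inclusion depends on a class A margin rated after the allocated crown is cemented, so the stated order of selection and randomisation is impossible and the 24-month comparison is no longer protected by randomisation

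*Protocol article*

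**What the plan says.** Under Inclusion criteria, one condition reads "The patient has received a class A assessment according to the modified US Public Health Service (USPHS) criteria for marginal adaptation after restoration". The section on the intervention group shows when it is judged. Step 1 makes the arm-specific preparation ("occlusal anatomical reduction of 2.0 mm will be performed to form a 90-degree rounded shoulder margin"), step 2 mills the crown, and in step 3 "Cementation, occlusion adjustment, and polishing will be performed". Step 4 then states: "Patients whose affected tooth receives a class A assessment according to the modified USPHS criteria of marginal adaptation will be included in this trial". For the flat arm, the control group section describes only a different first step and adds "The subsequent steps will be the same as those for the intervention group", so the same screen applies there.

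The randomisation paragraph, printed under Dropout criteria, gives another order: "Upon fulfilment of the selection criteria, 200 eligible participants will be randomly divided into intervention and control groups in a 1:1 allocation ratio".

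The abstract names marginal fit as the primary outcome. Outcome measures and Table 1 rate marginal adaptation from A to D at baseline and at 24 months. The dropout criteria are poor compliance and voluntary withdrawal. A margin below class A is not among them, and the article does not say how such a patient is counted.

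**The concern.** A condition for entry should be known before allocation and should not depend on the treatment received. This one can be known only after the allocated treatment has been delivered, and it is measured on the scale of the primary outcome. Every included patient starts at A by construction, and any allocated patient rated B, C or D at placement drops out of the trial.

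The two arms could lose different numbers of patients or different kinds of teeth. The Background says the two forms differ in bonding area and in remaining tooth tissue, so equal class A rates at placement cannot be taken for granted. The trial is open-label, so the rating that decides inclusion may be made with the arm known. The Hypothesis section claims superiority of the shoulder form's restorative effect. A comparison restricted to class A starts answers the narrower question of which margin deteriorates less once it has begun well.

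**Working it through.** **1. Order of events.** The randomisation paragraph gives: all selection criteria met, then allocation. Inclusion criteria and step 4 give: preparation in the arm's form, milling, cementation, class A rating, then inclusion. The rating needs a flat or shoulder crown in place, and the form is set by allocation. The class A criterion therefore cannot be met before allocation, and any workable order puts the screen after it.

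**2. The plan's own figure.** 160 / (1 − 0.20) = 200, or 80 / (1 − 0.20) = 100 per arm. This reproduces the stated recruitment target. The base figure of 160 cannot be rebuilt, because the article gives no effect size, rates or power. The point does not depend on it.

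**3. A real difference hidden (all rates assumed).** Let a be the share rated class A at placement. Let 15% of class A margins deteriorate by 24 months in both arms, and let margins below A at placement stay below A. The share below A at 24 months among all randomised is (1 − a) + 0.15a.

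| Class A at placement | Below A, all randomised | Below A, class A starts only |
|---|---|---|
| 95% | 0.05 + 0.1425 = 19.25% | 15% |
| 85% | 0.15 + 0.1275 = 27.75% | 15% |
| Difference | 8.5 points | 0 |

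With 97% versus 90%, the figures are 17.55% and 23.50%, a hidden difference of 5.95 points. With equal rates it is 0. Exchanging the arms reverses the sign.

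**4. A false difference created (all rates assumed).** Half the teeth are easy (95% of class A margins still A at 24 months) and half are hard (70%). The arm has no effect on 24-month status for a given tooth type. Easy teeth pass the screen in 95% in both arms. Hard teeth pass in 90% in one arm and in h in the other. The share still A among included patients is (0.5 × 0.95 × 0.95 + 0.5 × h × 0.70) / (0.5 × 0.95 + 0.5 × h). For h = 0.90 this is 0.76625 / 0.925 = 82.84%.

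| h in the other arm | Still A among included | Bias | Rejection at two-sided 5%, 80 per arm |
|---|---|---|---|
| 0.90 | 82.84% | 0 | 5.0% |
| 0.60 | 85.32% | 2.5 points | 7.1% |
| 0.50 | 86.38% | 3.5 points | 9.5% |
| 0.30 | 89.00% | 6.2 points | 20.3% |

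The rejection rates use a normal approximation for two proportions. For h = 0.30 the standard error is √(0.89 × 0.11/80 + 0.8284 × 0.1716/80) = 0.0548, and 0.0616 / 0.0548 = 1.12 standard errors, which gives 20.3%. This is a simplified A versus not-A comparison, not the planned Wilcoxon test. The arm that passes fewer hard teeth looks better.

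**5. Numbers, on one reading only.** Suppose 200 are randomised before the screen and those who fail it are not replaced. Then 100 × 0.95 × 0.80 = 76 and 100 × 0.85 × 0.80 = 68 remain, 144 in total against 160.

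**The case against.** The screen acts on the baseline rating, not on the 24-month rating. Durability is among the stated aims in the Objective section, so comparing deterioration from a sound start is partly within scope. No class A rate is given for either arm, and the bias is zero if the arms pass the screen alike within each tooth type. All of this stands. It limits what can be said about size, but it does not remove the contradiction or restore the protection of randomisation.

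Three stronger readings are tempting and are not supported.

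- **That the randomised comparison is lost.** The article shows that the comparison is unprotected, not that it is distorted.
- **That there is a second exclusion route in the shoulder arm only.** The Discussion says "the 90-degree shoulder endocrown is not suitable for all tooth restorations". That reads as a remark on clinical use of the results; no trial rule removes shoulder-arm teeth for unsuitability. The requirement for three or four intact walls and the exclusion of patients the researchers judge unsuitable can both be applied before allocation.
- **That the sample falls short.** The randomisation paragraph speaks of "Upon fulfilment of the selection criteria, 200 eligible participants will be randomly divided into intervention and control groups". On those words the 200 have already passed the screen, and 160 / 0.8 = 200 holds. A shortfall follows only if the screen comes after allocation without replacement, and the article is silent on replacement.

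Fig. 2, the schedule of enrolment and interventions, is not shown and might clarify when allocation occurs. It could not change the wording of the criterion or of step 4.

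**Conclusion.** The point holds as an error in stated rules, not as missing detail. The class A condition appears twice, is carried to the control arm, and cannot be reconciled with randomisation after selection. Following it means post-allocation selection on the baseline value of the primary outcome scale in an open-label trial. The 24-month result would then describe deterioration from a class A start and would not, by itself, support the superiority hypothesis.

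Neither the size nor the direction of the bias can be established from the article. Under the assumed rates above, the hidden difference runs from 0 to 8.5 points in either direction, and a true null is rejected in 5% to 20.3% of trials. The total of 144 against 160 is conditional on 200 being randomised before the screen, no replacement, and the same assumed 95% and 85% rates.

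An analysis plan could not repair this later, because it cannot recover outcomes for patients who were never included or followed.

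**What to change.** - Remove the post-restoration class A condition from the Inclusion criteria and step 4 of the intervention group section, which also removes it from the control arm.
- Reconcile both with the randomisation paragraph, so that all eligibility is settled before randomisation and randomisation precedes tooth preparation.
- Analyse every randomised patient in the assigned arm.
- Report the immediate post-cementation marginal grade by arm as an outcome, and keep the class A subset as a sensitivity analysis.
- Trial status says recruitment is under way. Identify any patients already randomised and then excluded for a margin below class A, and follow them to 24 months where feasible.

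For future patients the cost is an amendment to the eligibility wording and the order of steps. Baseline grades will no longer be identical by construction. Patients already excluded would need tracing and an added 24-month visit.
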